## Abstract

**Background:**

The atrial appendages are a tissue reservoir for cardiac stem cells. During on-pump coronary artery bypass graft (CABG) surgery, part of the right atrial appendage can be excised upon insertion of the right atrial cannula of the heart-lung machine. In the operating room, the removed tissue can be easily cut into micrografts for transplantation. This trial aims to assess the safety and feasibility of epicardial transplantation of atrial appendage micrografts in patients undergoing CABG surgery.

**Methods/design:**

Autologous cardiac micrografts are made from leftover right atrial appendage during CABG of 6 patients. Atrial appendage is mechanically processed to micrografts consisting of atrial appendage-derived cells (AADCs) and their extracellular matrix (ECM). The micrografts are epicardially transplanted in a fibrin gel and covered with a tissue-engineered ECM sheet. Parameters including echocardiography—reflecting cardiac insufficiency—are studied pre- and post-operatively as well as at 3 and 6 months of the follow-up. Cardiac functional magnetic resonance imaging is performed preoperatively and at 6-month follow-up. The primary outcome measures are patient safety in terms of hemodynamic and cardiac function over time and feasibility of therapy administration in a clinical setting. Secondary outcome measures are left ventricular wall thickness, change in the amount of myocardial scar tissue, changes in left ventricular ejection fraction, plasma concentrations of N-terminal pro-B-type natriuretic peptide (NT-proBNP) levels, New York Heart Association class, days in hospital, and changes in the quality of life. Twenty patients undergoing routine CAGB surgery will be recruited to serve as a control group.

**Discussion:**

This study aims to address the surgical feasibility and patient safety of epicardially delivered atrial appendage micrografts during CABG surgery. Delivery of autologous micrografts and AADCs has potential applications for cell and cell-based gene therapies.

**Trial registration:**

ClinicalTrials.gov Identifier: NCT02672163. Date of registration: 02.02.2016

## Background

Loss of functional myocardium after, for example, an ischemic insult instigates a need for the remaining tissue to undergo various levels of remodeling to compensate for the declining pumping efficacy. Dead tissue is replaced by non-contractile fibrous scar, while hypertrophy and dilatation may be prominent in other parts of the myocardium struggling to compensate for the lost pumping function. Despite improved drug therapies, many patients develop heart failure over time [1]. The prognosis of heart failure is poor; 4-year survival is less than 50%, and 40% of patients are dead or readmitted to hospital within the first year [2, 3]. Long-term survival has increased due to revascularization techniques such as coronary artery bypass grafting (CABG). Unfortunately, 25–30% of the operated patients do not respond to revascularization surgery by improved perfusion. These patients are thus in much higher risk of heart failure and death [4]. Economically, heart disease exerts a severe burden worldwide that is accentuated with population aging. In 2010, for example, heart disease cost the USA $316 billion [5].

During the last decade, cell-based therapies have entered the clinic with a new hope as therapy for heart failure. Several cell transplantation strategies have been evaluated in experimental as well as in clinical trials [6-8]. Consistent improvement in cardiac function has been reported in studies that have used cells of cardiac origin as the therapeutic cell population [9, 10]. Moreover, when patient’s autologous cells are used, the immune system is not activated to reject the cells, which are thus retained longer after transplantation. It has also been shown that enhancing vascular supply of nutrients together with cellular adherence to extracellular substrata further promotes the survival of transplanted cells [11].

In conjunction with revascularization surgery, the aim for cell therapy is to improve the functional recovery of the myocardial scar by restoring the cellular loss of the infarcted area. The cells for therapy need to be able to give rise to all structures of the myocardium. In principle, this means that the therapeutic cells must be capable of forming cardiac muscle (cardiomyocytes), supporting extracellular matrix (fibroblasts) and vasculature (endothelial and smooth muscle cells).

Cardiac-derived stem cells have higher potential to develop along cardiac lineage [7] and differentiate into cardiac myocytes [12] in vivo than the cells derived from other organs. Cardiac stem cells are self-renewing and multipotent, and they have high capacity to form clones and also enhance the differentiation of other progenitor cells to e.g. endothelial and smooth muscle cells. At least six types of stem cells have been isolated and characterized from the heart: Sca-1 cells [13], c-kit cells [14], islet-1 cells [15], cardiac side population cells [16], cardiosphere-derived cells [17], and ALDH(+) (aldehyde dehydrogenase) cells [18]. Cardiac stem cells can be found in abundance in the right atrial appendage [18, 19, 20] which thus represents an appealing source of tissue for cell therapy use.

The efficacy of cell therapy is decreased by the high rate of cell apoptosis soon after the transplantation. Numerous studies have focused on the different routes of the cell delivery. The most investigated approaches are intracoronary and intramyocardial injections and epicardial delivery. Animal models have proven the epicardial delivery to have advantages in securing adequate cell engraftment when compared to any kind of cell injections [21, 22].

Overall, cell-based therapies (by any delivery route) are regarded as safe to the patients [23]. For example, they have been shown to improve left ventricular function [23–26], quality of life, and physical activity tolerance [23, 25, 27]. However, further evidence on safety and feasibility of the epicardial delivery of cardiac stem cells is required.

The primary objective of this trial is to evaluate the clinical feasibility of intraoperative harvesting, processing, and transplantation of autologous atrial appendage tissue micrografts in terms of success in completing the delivery of the transplant to the myocardium in conjunction with cardiac surgery in the operating room as well as in terms of time restrictions associated with both transplant processing and cardiac surgery. Our primary objectives, in terms of safety, are to evaluate acute and 6-month cardiovascular parameters including rhythm, cardiac function, and need for vasoactive or inotropic medication. Our secondary objective is to obtain an initial insight into the therapeutic effect of atrial appendix micrograft transplantation as measured by baseline and 6-month follow-up cardiac functional MRI.

## Methods/design

### Patient selection

In all, 26 patients from the Helsinki University Hospital, Finland, will be recruited to the study in chronological order by the head researcher. Similar to our previous clinical cell therapy trial [28–31], patients of either gender will be initially evaluated for participation by the cardiologists. Patients with heart failure and scheduled for elective CABG are considered eligible for participation in the trial if they meet the inclusion criteria. The criteria for inclusion and exclusion of the patients are presented in Table 1. The first six patients will be recruited to the atrial appendage-derived cell (AADC) arm. Each patient is given both oral and written information about the trial, and the patient’s written informed consent is required for participation and obtained by the head researcher. After scheduling to surgery, patients will undergo a period of at least 4 to 8 weeks for optimization of drug therapy while waiting for the elective operation.

**Table 1 Tab1:** Inclusion and exclusion criteria for patients enrolled in the study

Criteria for eligibilty
Inclusion criteria
1 Stable coronary artery disease filling the criteria for bypass surgery 2 Age between 18 and 75 years 3 Informed consent obtained 4 LVEF between ≤ 45 and ≥ 20% 5 NYHA class II–IV heart failure symptoms
Exclusion criteria
1 Heart failure due to LV outflow tract obstruction 2 History of life-threatening ventricular arrhythmias or resuscitation, a condition possibly repeating, or an implantable cardioverter-defibrillator 3 Stroke or other disabling condition within 3 months before screening 4 Severe valve disease or scheduled valve surgery 5 Renal dysfunction (GFR < 84 ml/min/1.73 m) 6 Other disease limiting life expectancy 7 Contraindications for coronary angiogram or MRI 8 Participation in some other clinical trial

*LVEF* left ventricular ejection fraction, *NYHA* New York Heart Association, *LV* left ventriculum, *GFR* glomerular filtration rate

Echocardiography (ECHO), quality of life (QoL) questionnaire (standardized SF-36 health survey questionnaire), New York Heart Association (NYHA) class, basic laboratory tests, and N-terminal pro-B-type natriuretic peptide (NT-proBNP) from blood are all evaluated at baseline as well as at 3 and 6 months of the follow-up. Blood RNA and EDTA plasma samples are taken at the pretrial and at 6 months of the follow-up to search markers for prognostic factors. Cardiac MRI is performed at the pretrial and at 6 months of the follow-up.

To determine the safety of the procedure, the next 20 patients who meet the same inclusion and exclusion criteria and are scheduled for elective CABG operation are recruited to the study as control patients. These patients are treated according to the normal hospital protocol, without the extracellular matrix (ECM) sheet and any additional imaging, examination, or blood tests required for the AADC therapy group. Written consent is obtained also from the control patients.

### Cell isolation

During CABG surgery, autologous cardiac cells are harvested from a leftover right atrial appendage tissue that is removed for insertion of the heart-and-lung machine. This material serves a safely removable source for cardiac cells. However, quality of the tissue varies greatly between the patients: atrial fibrillation and dilatation as well as diabetes mellitus and obesity may cause accumulation of connective and adipose tissue [32–34], which decrease the quality of the appendage tissue. Also, the size of appendage differs between patients according to age and gender. To standardize the amount of tissue removed for harvesting, the size of removable appendage is 5 × 10 mm and the weight from 600 to 800 mg. The harvested tissue is processed on site in the operating room using a cell therapy tissue homogenizer (Rigenera System, HBW s.r.l., Turin, Italy) (Fig. 1a (A)) [35]. The device is CE-marked and in clinical use for isolation of therapeutic cells from a skin biopsy to treat hard-to-heal or chronic wounds. This system enables extraction of 5–10 millions of single cells per gram of atrial appendage tissue. In addition to these single cells that can be counted, the mixture contains a vast number of cell clusters, i.e., micrografts containing many interconnected cells attached to their extracellular matrix, raising the estimated cell number to reach at least 60 million viable cells per gram of tissue. The isolation of the cells can be performed with ease and strict adherence to sterility in the operating room by a nurse who has received basic training in using the instruments. Initial training was carried out in a cell culture laboratory, and the protocol to accompany CABG surgery was further trained in a large animal model. This cell isolation technology is a straightforward approach for administering autologous cell therapy in a routine and safe manner during surgical procedures. The system utilizes a sterile, single-use tissue homogenizer surface to generate the micrografts.

**Fig. 1 Fig1:**
[figure not shown]
**a** Preparing the AADC-sheet. (A) The atrial appendage tissue is processed with cell therapy tissue homogenizer (Rigenera-system). (B) The micrografts are secured to extracellular matrix sheet (Cormatrix®) by using a fibrin sealant (Tisseel™). (C) The AADC sheet is placed to the myocardium in the location of infarction scar (animal model). **b** Administration of therapy during CABG surgery. Figure reproduced from our article by Lampinen et al. (Current Gene Therapy, 2015)

The isolated AADC micrografts are applied in within cardioplegia suspension as a composite graft on the damaged myocardium using the epicardial transplantation technique. Firstly, the suspension of autologous, freshly isolated AADCs are applied onto the extracellular matrix sheet (Cormatrix® ECM™ Technology, Cormatrix Cardiovascular Inc., Atlanta, GA, USA). Fibrin sealant (Tisseel™, Baxter Healthcare Corp. Westlake Village, CA, USA), routinely used in surgery for hemostasis and tissue sealing, will be added into the cell suspension in order to secure the adherence of the suspension to the matrix (Fig. 1a (B)). Then, the matrix sheet is placed on top of the damaged myocardium. Administration of the transplant is presented in Fig. 1b. The Cormatrix® readily attaches to the tissue but will be further secured to the myocardial surface by suturing (Fig. 1a (C)).

### Therapy administration

A standard CABG operation is performed under cardiopulmonary bypass and mild hypothermia. The operations take place under cardiac arrest and cardioplegia protection. After completion of the bypass anastomoses, each patient receives, under cardiac arrest, a Cormatrix® patch containing autologous cells in physiological saline and fibrin sealant on the infarction area. The area of application is selected before surgery by using the pre-CABG MRI imaging data. The therapy application procedure is carefully photographed during each surgery, and the treatment administration site is specified in patient documents for analysis.

### Clinical cardiac MRI

Cardiac MRI is performed with a 1.5T Avanto fit scanner and phase array cardiac coil (Siemens, Erlangen, Germany). Images will be obtained with electrocardiography (ECG) gating and during breath-holding. LV structure and function are imaged by a standardized MRI protocol [36]. TrueFISP cine series is obtained at the vertical and horizontal long axes for scout to line up short-axis images. The stack of short-axis images is obtained from the mitral valve plane through the apex. To detect the myocardial scar, late gadolinium enhancement (LGE) is imaged with a 2D-segmented inversion recovery gradient ECHO sequence 12 to 20 min after Dotarem® (279.3 mg/ml; dose 0.2 mmol/kg) injection. LGE images are obtained at the same views and slice/gap thickness as cine imaging.

### End-point measures

Table 2 lists the outcome measures of the trial. Specifically, the primary outcome measures are patient safety in terms of hemodynamic and cardiac function and feasibility of the therapy administration in a clinical setting. Hemodynamics is evaluated during the operation and stay at the intensive care unit (ICU) by the need for vasoactive medication and success of weaning from cardiopulmonary bypass and respirator. Postoperative hemodynamic criteria for assessing safety are cardiac index, hemoglobin, SvO_2_, serum potassium level, and blood glucose level. Cardiac function is evaluated also during the operation by transesophageal ECHO and during the stay at ICU by transthoracical ECHO as well as telemetric monitoring of rhythm. Feasibility is evaluated by the success in completing the delivery of the cell sheet to the myocardium, waiting times in minutes for either the cell sheet or the heart after finishing anastomoses, and the success in closing the right atrial appendage by purse string suture without additional sutures or patching.

**Table 2 Tab2:** Primary and secondary outcome measures

Primary outcome measures	Secondary outcome measures
Safety	Preliminary efficacy
For assessing hemodynamics during the operation and at the intensive care unit	For assessing cardiac function and remodeling as measured by MRI
1. Need for vasoactive medication	1. Left ventricular wall thickness
2. Cardiac index in l/min/m^2^	2. Change in the amount of myocardial scar tissue
3. Hemoglobin in g/l	3. Change in left ventricular ejection fraction
4. Oxygen saturation in the pulmonary arterial blood (SvO_2_) in %	4. Change in movement and diastolic function of left ventricular wall
5. Serum potassium level in mmol/l	Others
6. Blood glucose level in mmol/l	1. Plasma concentrations of N-terminal pro-B-type natriuretic peptide (NT-proBNP) levels
For assessing cardiac function during and after the operation by echocardiogram	2. New York Heart Association class
7. Left ventricular ejection fraction (EF) in %	3. Days in hospital
8. Pericardial effusion in mm	4. Changes in the quality of life measured by questionnaire
For assessing cardiac function after the operation	
9. Telemetric monitoring of rhythm	
Feasibility	
1. Success in completing the delivery of the transplant to the myocardium	
2. Waiting time in minutes for the finished transplant to be placed on the myocardium after doing all the required anastomoses	
3. Waiting time in minutes for the heart after doing all the anastomoses and before the transplant is finished	
4. Closing the right atrial appendage after removing the standardized tissue piece for preparing the transplant	

The secondary outcome measures are change in LV wall thickness and movement and diastolic function as measured by MRI, change in the amount of myocardial scar tissue as measured by MRI, local changes in systolic and diastolic measures as estimated by ECHO, changes in left ventricular ejection fraction (LVEF), pro-BNP level, NYHA class, hospitalization or the days in hospital, and QoL.

Figure 2 presents the timeline of the study indicating enrollment and follow-up as well as timing of laboratory tests, MRI, and echocardiographic imaging for each patient.

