### Statistical analysis

Statistical methodology as published previously by Pätilä et al. [28] will be utilized. Briefly, the Mann-Whitney *U* test will be used for non-parametric continuous variables and results will be reported as median with interquartile range (IQR). Categorical variables will be analyzed using Fisher’s exact test. Intra-observer variability will be assessed using the Bland-Altman method. Testing for *p* values will be carried out two-sided with *p* < 0.05 considered statistically significant. Results should be treated as preliminary due to the small sample size and will be presented with 95% confidence intervals. A sample size of 26 has been shown to be sufficient in our previous studies to demonstrate safety. Computation will be achieved with PASW Statistics (IBM Inc., Armonk, NY) or equivalent software.

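### Weaning from bypass and respirator is a safety criterion in the text but absent from Table 2, and scored only as success it cannot show delay in patients who are eventually weaned

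*Protocol article*

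**What the plan says.** The protocol article, under "End-point measures", states that "the primary outcome measures are patient safety in terms of hemodynamic and cardiac function and feasibility of the therapy administration in a clinical setting". It then says that hemodynamics during the operation and the ICU stay is evaluated "by the need for vasoactive medication and success of weaning from cardiopulmonary bypass and respirator". It attaches no duration, number of attempts or time limit to that success.

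The same paragraph does use a time scale for feasibility, where it asks for "waiting times in minutes for either the cell sheet or the heart after finishing anastomoses".

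The section opens with "Table 2 lists the outcome measures of the trial". Table 2 has nine safety items: vasoactive need, cardiac index, hemoglobin, SvO2, potassium, glucose, echocardiographic ejection fraction, pericardial effusion and rhythm. Weaning from bypass or from the respirator is not among them.

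Under "Statistical analysis", the sentence beginning "Categorical variables will be analyzed using Fisher" sends yes/no outcomes to the exact test, and continuous outcomes go to the Mann-Whitney U test. Both are two-sided at 0.05. Results are to be called preliminary and given with 95% confidence intervals.

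The arms are sequential: "The first six patients will be recruited to the atrial appendage-derived cell (AADC) arm", and controls are "the next 20 patients who meet the same inclusion and exclusion criteria".

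**The concern.** There are two linked problems.

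- **Status.** The text uses weaning to judge primary safety, while the table that is said to list the outcomes leaves it out. An analyst working from the table would not report it; one working from the text would.
- **Scale.** Success is naturally a yes/no score. With no time limit, a patient extubated after 6 hours and one extubated after 6 days score the same. If the graft slowed recovery without preventing it, this item would read as no difference between the arms. That holds at any success rate, because delay is simply not part of the score.

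The Discussion makes the move to efficacy trials depend on there being no disturbance of rhythm, hemodynamics or cardiac function. A hemodynamic item that cannot register delay adds reassurance without adding information.

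**Working it through.** **Inputs from the article:** 6 treated, 20 control, two-sided 0.05, Fisher for categorical and Mann-Whitney for continuous outcomes. The stated total of 26 agrees with 6 + 20. It comes with no effect size, event rate, SD or power, so it cannot be reproduced further.

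**Step 1. How many failures Fisher's test needs (no assumptions).** Two-sided p sums the tables that are no more probable than the one observed.

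- 1/6 v 0/20: 6/26 = 0.231.
- 2/6 v 0/20: C(6,2)/C(26,2) = 15/325 = 0.046.
- 2/6 v 1/20: (15×20 + 20)/C(26,3) = 320/2600 = 0.123.
- 3/6 v 1/20: (20×20 + 15)/C(26,4) = 415/14950 = 0.028.

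So at least 2 of 6 treated patients must fail if no control fails, and 3 of 6 if one control fails. If all six are weaned, the exact 95% upper limit for the treated failure rate is 1 − 0.025^(1/6) = 46%.

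**Step 2. Delay with eventual failure unchanged (failure rates assumed).** By exact enumeration over 6 v 20, the chance of a significant result in the direction of harm is 0.1%, 0.4% and 1.3% when eventual failure is 1%, 2% and 5% in both arms. The chance that none of the 26 fails is 0.99^26 = 77%, 0.98^26 = 59% and 0.95^26 = 26%. Even if failure itself rises from 5% to 10%, the chance of a significant result is 4.7%.

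**Step 3. The same delay on three scales.** Assumed, and not in the documents: log-normal ventilation time, control median 8 h, treated median 16 h, log-SD 0.6, 0.8 or 1.0. The proportion beyond a limit L is 1 − Φ[ln(L/median)/SD].

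- *Open-ended success*, with failure taken for illustration as still ventilated at 7 days (168 h). The ratios are ln(21)/SD for control and ln(10.5)/SD for treated. At SD 0.6 and 0.8 failure is below 0.2% in both arms. At SD 1.0 it is 0.1% v 0.9%. Fisher power is at most about 0.1%.
- *Success within 24 h*, with ratios ln(3)/SD and ln(1.5)/SD, for illustration only:

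| log-SD | control failing | treated failing | Fisher power |
|---|---|---|---|
| 0.6 | 3.4% | 25.0% | 30% |
| 0.8 | 8.5% | 30.6% | 22% |
| 1.0 | 13.6% | 34.3% | 15% |

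- *Hours*, exact Mann-Whitney test, by simulation: about 61–62% at SD 0.6, 39–41% at 0.8 and 26–28% at 1.0. The ranges are scatter between simulation runs.

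**Step 4. What hours would let the report say.** By a normal approximation, the 95% interval for the ratio of medians spans a factor of exp[1.96 × SD × √(1/6 + 1/20)] either way: 1.73, 2.07 and 2.49 at SD 0.6, 0.8 and 1.0. If the observed medians were equal, a doubling would be excluded at SD 0.6 but not at 0.8 or 1.0.

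**The case against.** The case on the other side is substantial, and much of it stands.

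- **Other measures can react.** A reader might infer that the safety conclusion rests on a criterion that cannot move. The article does not support that. Vasoactive need, cardiac index, SvO2, echocardiography and rhythm are all primary, seven of the nine safety items in Table 2 carry numeric units, and days in hospital is a graded secondary outcome. None of them measures time to weaning, but several bear on a weaker heart.
- **The ceiling is assumed.** It is tempting to say that nearly every patient in both arms will be weaned. No weaning rate or ventilation time appears in the article, and patients have an ejection fraction of 20–45% and NYHA class II–IV. The statement that an open-ended score cannot register delay does not need this premise; the power figures do.
- **The full protocol may define success.** A condensed article can leave the definition to it, so the missing definition is not the complaint. The point is the choice of a success score. On the assumptions above, a 24-hour limit would recover only part of what hours carry.
- **Routine availability.** One might claim that weaning is one of few primary criteria charted in both arms. The article says that controls have none of the additional tests, but not which primary measures are routine, so that claim is dropped.
- **The alternative is imperfect.** Extubation time depends on ICU practice and unmasked staff, and the arms are recruited one after the other. Failure to separate from bypass is less open to discretion. This is a reason to keep the failure count, not to do without the times.

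**Conclusion.** The point holds in a limited form. Two parts rest on the article alone: text and Table 2 disagree on whether weaning is an outcome, and a yes/no weaning score with no time limit cannot show delay in patients who are eventually weaned. The Fisher thresholds (2/6 against 0/20, 3/6 against 1/20) also need no assumption.

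The size of the loss does rest on assumptions: a doubling from 8 to 16 h, log-normal times and a log-SD of 0.6 to 1.0. Within them, power is about 0% for open-ended success, 15–30% with a 24-hour limit and about 26–62% for hours. Hours are clearly more informative, but with six treated patients they still miss a doubling more often than not once the log-SD reaches 0.8. No figure is computed here for separation from bypass; the argument there is by analogy. This is a low-cost improvement and does not invalidate the trial's safety assessment.

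**What to change.** Reconcile "End-point measures" with Table 2 by adding weaning to the table's safety items, in this form:

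1. **Failure to wean** from bypass or from the respirator: keep success/failure, with each failure listed individually.
2. **Minutes to final separation from bypass** (for example from release of the aortic clamp) and **hours from ICU admission to final extubation**, both taken from routine charts in both arms.
3. **Ranking:** patients who are never weaned, or who die before weaning, receive the worst rank.
4. **Reporting:** median, IQR and 95% confidence interval, compared with the Mann-Whitney test already planned. If worst-ranked patients leave a quartile or confidence limit without a numeric value, say so.

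The cost is a change of outcome wording and two chart times per patient. It needs no added test for the controls and no change to care. State two caveats beside the result: extubation time also reflects ICU practice and unmasked staff decisions under sequential allocation, and at 6 v 20 a non-significant difference does not show that weaning was not delayed.
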